## Abstract

**Introduction::**

Current total hip arthroplasty (THA) implant usage trends favor cementless fixation, and plenty studies have demonstrated that numbers of cementless femoral stems are associated with excellent long-term survivorship and functional outcomes. Various types of cementless femoral stems have been developed and utilized in multiple applications, including straight, tapered, anatomic, customized, short, and even neck stems. All of these designs aimed to achieve maximal primary stability and promote osseointegration. Nevertheless, stress-shielding and periprosthetic bone loss continue to occur and remain critical issues in promoting long-term survivorship of THA. Considering anatomic and tapered stems are the most popular cementless designs today, this prospective cohort study aimed to investigate the effect of stem design on stress-shielding and periprosthetic bone remodeling after implantation of an anatomic stem with proximal fixation (Ribbed Hip system; Waldemar Link, Hamburg, Germany) and the direct comparison to a fully coated tapered stem (LCU Hip system; Waldemar Link).

**Materials and methods::**

This prospective cohort study will comprise patients who receive primary unilateral THA with the Ribbed anatomic hydroxyapatite (HA)-coated stem or LCU tapered fully HA-coated stem. The changes in periprosthetic bone mineral density after insertion of Ribbed and LCU stem prostheses will be assessed by means of dual-energy X-ray absorptiometry in the periprosthetic region of interest according to Gruen and colleagues. Standard anteroposterior and lateral plain radiography will be performed for qualitative assessment of the periprosthetic bone remodeling. The following items will be analyzed or measured on follow-up radiographs to compare with the initial appearance on the radiographs taken immediately postoperatively: cortical thickness in each Gruen zone, fitness of the distal stem within the isthmus, femoral stem alignment, radiolucent line, reactive line, periosteal bone reactions, and subsidence. Biologic fixation and stability of the cementless implant will be evaluated using Engh grading scale, and heterotopic ossification will be graded according to Brooker classification. Furthermore, Harris hip score and Western Ontario and McMaster Universities Osteoarthritis Index Score will also be assessed for postoperative functional evaluation. These radiologic and clinical assessments will be taken postoperatively, at 6 months, 1, 2, 3, 4, and 5 years after surgery.

**Ethics and dissemination::**

This study was approved by The First Affiliated Hospital of Chongqing Medical University Ethics Committee. The study results will be disseminated at national and international conferences and published in peer-reviewed journals.

**Study registration::**

Chinese Clinical Trial Registry (http://www.chictr.org.cn): ChiCTR1800017841.

## Introduction

1

During the past decade, a growing body of evidence supports the use of cementless femoral stems with many studies indicating excellent track record that includes high long-term survival rate and satisfying functional outcomes.^[1–6]^ Therefore, cementless femoral prostheses have become the predominant stem utilized in the United States.^[7]^ However, along with the global trends in population aging and longer life expectancy, and increasing number of total hip arthroplasty (THA) is performed in younger, healthier, and more active patients, the expectations regarding THA are continuously rising, in particular regarding the high durability and long-term survival.^[8–13]^ Clinical longevity of cementless implants mainly depends on the osseointegration; however aseptic loosening, the clinical endpoint of bone resorption around the implant, remains the principle cause of implant failure.^[14–16]^ Stress shielding, an unavoidable mechanical phenomenon after insertion of the femoral stem into the intramedullary canal, has been identified as the primary factor contributing to adaptive periprosthetic bone remodeling and resorption around hip stems.^[17–20]^ Stem geometry of the implant plays a crucial role in the load transfer to the femur and consequently bone adaption, thus optimization of geometry could reduce stress shielding, minimize bone atrophy, and promote long-term survivorship.^[21,22]^

Currently, various types of cementless femoral stems have been developed and utilized in multiple applications, and according to the basic design concepts of cementless femoral stems, the main rationales in stem geometry can be initially classified into 3 types: anatomic designs, straight designs, and tapered designs.^[23–25]^ Recently, customized stems, short stems, and neck stems have been developed to reduce stress shielding and improve long-term stability.^[26,27]^ Each type of design has distinct geometries and philosophies, accompanied with a unique model of load transfer and stress-shielding, which would induce implant-specific periprosthetic bone remodeling.^[28,29]^ Therefore, prospective long-term follow-up of the periprosthetic bone mineral density (BMD) changes would help to evaluate the stress shielding, understand the periprosthetic bone remodeling, which is critical for improving the design of implants, predicting periprosthetic fracture or loosening, and aiding in clinical decisions.

Considering anatomic stems and tapered stems are the most popular cementless designs in primary THA today, and comparison of periprosthetic bone remodeling after implantation of anatomic and tapered cementless femoral stems in THA is relatively limited, we thus designed this prospective cohort study, which aimed to investigate the effect of stem geometry on stress-shielding and periprosthetic bone remodeling after implantation of an anatomic stem with proximal fixation (Ribbed Hip system; Waldemar Link, Hamburg, Germany) and the direct comparison to a fully coated tapered stem (LCU Hip system; Waldemar Link).^[30–33]^

## Materials and methods

2

This study will be performed and reported in accordance with the STrengthening the Reporting of OBservational studies in Epidemiology (STROBE) checklist.^[34]^

### Study design

2.1

This is a 5-year prospective longitudinal cohort study, which will be conducted in The First Affiliated Hospital of Chongqing Medical University. It will start recruiting patients in September 2018 and is being prepared now. The study will be executed in 2 phases. Phase I is a cross-sectional study, which will be conduct during hospitalization to obtain the baseline data; phase II comprises a cohort follow-up study at 6 months, 1, 2, 3, 4, and 5 years after THA. Participants will be followed for at least 5 years, or until death.

### Participants and eligibility criteria

2.2

Adult patients who undergone primary unilateral THA with the Ribbed (Ribbed Hip system; Waldemar Link) cementless anatomic hydroxyapatite (HA) coated femoral stem or LCU (LCU Hip system; Waldemar Link) cementless tapered fully HA-coated femoral stem will be potential eligible for this study. However, subjects who meet any of the following criteria will be excluded from the study: with abnormal deviations of the femoral neck (varus caput-collum-diaphysea [CCD] angle <115°, valgus CCD angle >150°) or other femoral deformities; diagnosed with intertrochanteric fractures or pathologic fractures; or diagnosed with bone tumor, glucocorticoid, hyperthyroidism, hypothyroidism, or any other diseases that affecting bone metabolism. Furthermore, subjects who opt to terminate participation or want to withdraw from the research will be discontinued from the study. The participant who has been withdrawn will be replaced by a new participant if time permits.

### Surgical procedures

2.3

All surgeries are routinely performed by 2 senior surgeons using posterior-lateral approach under general anesthesia in laminar air flow operation room. Surgeons conduct the preoperative design on the equal proportion digital radiography according to the prosthesis template to predict implant type and size. During the operation phase, the femoral neck will be fully exposed, and the femoral head will be removed by osteotomy under the condition of retaining moderate femoral calcar. Acetabular preparation and implantation of a cementless cup followed standard procedures. Then, the assistant will adduct and internally rotate the hip joint to reveal the end of the femoral neck, and the medullary cavity will be enlarged with reamers of increasing sizes, and the appropriate type of components model will be selected and installed according to the size of it. A definite implant matching the size will be inserted using a handle. Perioperative intravenous of antibiotic cefuroxime and postoperative rivaroxaban are routinely used in prevent of infection and thrombosis provided that no contraindications existed. Intravenous combined with topical tranexamic acid are sequentially used to reduce blood loss and transfusions. Patients will be mobilized using standard physiotherapy program, and immediate full weight-bearing with crutches will be encouraged from the 1st postoperative day.

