### Statistical analysis

2.8

Frequencies and percentages will be estimated for qualitative data, and mean value ± SD will be calculated for quantitative data. To compare the periprosthetic BMD changes of Gruen zones between the Ribbed and LCU stems, statistical analysis will be performed using the Student *t* test for unmatched pairs to examine the significance of BMD changes of ROI 1–7, at each follow-up time point. And for further description of periprosthetic BMD changes, mean average BMD changes of ROI 1–7 will be presented as difference of both absolute and relative values (%) referred to the postoperative measurement. To minimize potential influential factors and better understanding the periprosthetic bone remodeling, we will also compare the periprosthetic BMD changes between the prosthetic side to the contralateral side by a paired *t* test for the Ribbed and LCU stems, respectively. For all analysis, a 2-tailed value of *P* < .05 is defined as statistically significant. Statistical analysis will be performed using the software SPSS version 22.0 (IBM Corporation, Armonk, NY).

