## Discussion

3

A variety of implant-, surgery-, and host-related factors have been delineated to explain the development of aseptic loosening and periprosthetic bone remodeling.^[45–47]^ The stem geometry is believed to play an important role in the load transfer to the femur, and consequently, in femoral remodeling and osseointegration.^[21,48]^ Dozens of previously published studies have reported the periprosthetic BMD changes following THA, but comparison of anatomic and tapered cementless femoral stems are rather limited.^[28,30,31,49–52]^ To the best of our knowledge, this will be the 1st study to compare the periprosthetic bone remodeling between the Ribbed and LCU stems. Although computer-simulation models like finite element analysis have been developed to calculate stress distribution, predict the extent of stress shielding, and long-term adaptive bone remodeling, the actual stress shielding and bone adaption in real-world working environments probably vary considerably, mainly because bone remodeling not only depend on mechanical factors but also more on biologic and physiologic ones.^[18,53–55]^ Therefore, periprosthetic BMD changes remain the optimal method available to reflect the long-term multi-factors involved bone remodeling.

The major limitation of this study is the technology limitation of DXA, which is unable to provide additional information about cortical and trabecular bone, and bone microarchitecture. The separate quantification of trabecular and cortical bone allows a better understanding of how bone is lost or formation in different regions, and future periprosthetic bone remodeling research using HRpQCT-technique-based BMA are warranted.^[35,56]^

In conclusion, this study will greatly contribute to a better understanding of the stem geometry and periprosthetic bone remodeling. The findings of this study would be valuable for improving the design of implants, and will act as a guide for the revolutionary of prosthesis designs.

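### The non-randomised Ribbed versus LCU comparison rests on an unadjusted t test, so differences between patients or surgeons can appear as a stem effect

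*Protocol article*

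**What the plan says.** - **Design.** Section 2.1: "This is a 5-year prospective longitudinal cohort study". Section 2.2 defines the groups by the implant received: "Adult patients who undergone primary unilateral THA with the Ribbed" stem, or with the LCU stem. No randomisation, matching or allocation rule is described.
- **Aim.** The Introduction states that the study "aimed to investigate the effect of stem geometry on stress-shielding and periprosthetic bone remodeling".
- **Implant selection.** Section 2.3 has two senior surgeons template on the radiograph "according to the prosthesis template to predict implant type and size". After the canal is reamed, "the appropriate type of components model will be selected and installed according to the size of it".
- **Between-stem analysis.** Section 2.8: "statistical analysis will be performed using the Student *t* test for unmatched pairs", applied to BMD change in each of seven zones at each visit. No covariate, stratification or propensity method is named.
- **Other comparison.** Section 2.8 adds a paired t test of the operated against the contralateral side, run separately for each stem and offered as a way to limit other influences.
- **Limitations.** The Discussion accepts that surgical and host factors contribute to remodeling. It then says "The major limitation of this study is the technology limitation of DXA" and does not mention non-random stem choice.

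**The concern.** An unpaired t test on its own supports a causal reading only if the two groups would have lost the same bone on average had they received the same stem. Nothing in the design secures this. Canal shape, bone quality, age, sex, diagnosis and surgeon could each differ between the groups and also affect later BMD change. Any such factor shifts the estimated stem difference, and the P value takes no account of the shift. The article intends its findings to inform implant design, so a patient difference mistaken for a stem difference would matter.

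**Working it through.** The article gives no figure for confounding, so there is none to reproduce. The check has two parts.

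**1. Does any stated feature remove confounding between the stems?**

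- *Exclusions (section 2.2).* Extreme neck-shaft angles (below 115° or above 150°), femoral deformity and bone-metabolic disease are removed. This narrows the range of anatomy and bone quality but leaves variation inside it.
- *Change from the 2-day scan (section 2.8).* This removes differences in BMD level. It does not remove differences in the rate of change linked to age, sex, bone quality, canal shape or surgeon.
- *Contralateral paired test (section 2.8).* It is done within each stem and does not compare the stems.

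Each helps in part at most.

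**2. How large could the effect be?**

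Inputs from section 2.7: SD 0.2 g/cm², planned difference 0.1 g/cm², 50 per group, 20% dropout. Completers: 50 × (1 − 0.20) = 40 per group. The SD comes from an earlier cross-sectional study of Ribbed patients. Using it as the SD of BMD change is an assumption.

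Assumed, because the documents give neither: one factor differs between groups by *m* SD and has within-group correlation *r* with BMD change. There is no true stem effect.

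- Spurious difference = *m* × *r* × 0.2.
- Standard error = 0.2 × √(2/40) = 0.0447.
- False-positive rate: two-sided 5% t test, 78 degrees of freedom, noncentrality = spurious difference / 0.0447.

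| m (SD) | r | Spurious difference (g/cm²) | Noncentrality | False-positive rate |
|---|---|---|---|---|
| 0 | any | 0 | 0 | 5% |
| 0.5 | 0.3 | 0.030 | 0.67 | 10.2% |
| 0.5 | 0.5 | 0.050 | 1.12 | 19.7% |
| 0.8 | 0.3 | 0.048 | 1.07 | 18.5% |
| 0.8 | 0.4 | 0.064 | 1.43 | 29.3% |
| 0.8 | 0.5 | 0.080 | 1.79 | 42.4% |

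Against the planned 0.1, the spurious difference is 0.03/0.1 = 30% to 0.08/0.1 = 80%.

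A simulation with 4,000 runs at each of the four corner settings (*m* 0.5 or 0.8, *r* 0.3 or 0.5) gave unadjusted rates of 10.8% to 42.2%. With the factor in a linear model, the rate was 4.8% to 5.7%. This is the ideal case: the factor is measured without error and acts linearly.

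**Effect of adjustment on precision.** Adjusting for one factor multiplies the variance of the stem estimate by about (1 − *r*²)(1 + *m*²/4):

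- *m* 0.5, *r* 0.3: 0.91 × 1.0625 = 0.967, equivalent to 40/0.967 = 41.4 per group.
- *m* 0.5, *r* 0.5: 0.75 × 1.0625 = 0.797, equivalent to 50.2.
- *m* 0.8, *r* 0.3: 0.91 × 1.16 = 1.056, equivalent to 37.9.
- *m* 0.8, *r* 0.5: 0.75 × 1.16 = 0.870, equivalent to 46.0.

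Precision can therefore improve or worsen. The case for adjustment is bias.

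**The case against.** **Section 2.3 may only describe sizing.** The phrase about selecting a component follows reaming and precedes a sentence on inserting a definitive implant of matching size. It can be read as fitting a component to the canal. The templating phrase does separate type from size, but it names neither stem, and cup models also vary (section 2.4). This stands. A reader might infer that surgeons choose between Ribbed and LCU on femoral anatomy, and the article does not establish that. The groups are non-randomised on either reading.

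**Bias is not shown.** This also stands. A reader might infer that bone differences will be reported as stem effects. The documents give no imbalance or correlation, and imbalance may be small or absent.

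**The article is condensed.** A covariate list could sit in a fuller plan. But the article names the between-stem test itself, and that test does not fit the stated aim.

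**Baseline adjustment is not clean.** The 2-day scan of the operated side follows reaming and implantation, in zones defined from each stem's first postoperative image (section 2.5). It may depend on the stem. This stands and shapes the repair.

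**Adjustment as a precision gain.** A reader might compute 40/(1 − *r*²) = 44.0 to 53.3 and credit adjustment with 4 to 13 extra patients per group. That holds only if the covariate is balanced, which contradicts the imbalance behind the bias figures.

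**Conclusion.** The point holds in a limited form. The article fixes an unadjusted test as the only between-stem analysis in a non-randomised cohort with a causal aim, and does not clearly state how stems are assigned. Patient and surgeon differences can therefore appear as stem effects, and the exclusions, change scores and contralateral test reduce this only in part.

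The figures illustrate what could happen and do not predict it. The range of 0.03 to 0.08 g/cm² and about 10% to 42% rests on *m* of 0.5 to 0.8 SD, *r* of 0.3 to 0.5, SD 0.2 and 40 completers per group. The direction is unknown. The change is worth making because a better-suited method is available at little cost.

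**What to change.** 1. **Section 2.8, primary between-stem comparison.** Use a linear model of zone BMD change on stem, adjusted for factors the stem cannot have altered: age, sex, BMI, diagnosis, surgeon, a canal-shape index read from the existing templating radiograph, and the contralateral 2-day BMD that section 2.5 already measures.
2. **Sensitivity analysis.** Add the operated-side 2-day BMD for that zone as a covariate, noting that it is taken after implantation.
3. **Unadjusted t test.** Keep it as descriptive.
4. **Sections 2.2 and 2.3.** State how each patient comes to receive one stem or the other, and clarify whether the type chosen in section 2.3 refers to the stem system.
5. **Discussion.** Name non-random stem choice as a main limitation and report adjusted associations.

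**Cost.** Revised wording, one extra measurement on an existing image, and routine recording of the listed covariates. The model uses about 7 further degrees of freedom if diagnosis is held to two categories, leaving 80 − 2 − 7 = 71 with 40 completers per group. Precision may fall somewhat if covariates are imbalanced. Confounding by unmeasured or poorly measured factors remains and must be stated.

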### Implant

2.4

The Ribbed anatomic stem employs an anatomically s-shaped geometry, which permits the insertion of the greatest possible stem size into the medullary canal, thus achieving the aimed at form closure distally and proximally (Fig. 1). The broad prominent proximal ribs achieve a close fit to the supporting bone mass to provide the implant proximal fixation. While the LCU tapered stem employs a straight stem with tapered lateral shoulder, which is straight with a rectangular cross-section to give the implant proximal stability (Fig. 2). Both stems are made from forged titanium alloy (Ti6Al4V, Tilastan; Waldemar Link), the proximal portions of the Ribbed stem and the whole length of the LCU stem are provided with an osteoconductive calcium phosphate layer (HX Coating, about 15 μm thick). The detailed similarities and differences in the biomechanical properties between the Ribbed and LCU stems are listed in Table 1.

**Figure 1 F1:**
[figure not shown]
Ribbed cementless anatomic femoral stem (Ribbed Hip system, Waldemar Link, Hamburg, Germany).

**Figure 2 F2:**
[figure not shown]
LCU cementless tapered femoral stem (LCU Hip system, Waldemar Link, Hamburg, Germany).

**Table 1 T1:**
[figure not shown]
Comparison of anatomic (Ribbed Hip system) versus tapered (LCU Hip system) femoral stem design.

Both Trabeculae Oriented Pattern (TOP Acetabular Cup System; Waldemar Link) and TOP II (TOP II Acetabular Cup System; Waldemar Link) cementless hemispheric cup with a highly crosslinked polyethylene liner are used in both groups. Both metal-on-polyethylene and ceramic-on-polyethylene bearing surfaces are used; and majority of femoral head used in primary THA measuring 28 mm, larger diameter femoral head (32 mm) is seldom used.

### Primary outcome measurement

2.5

The primary outcome in the present study is periprosthetic BMD changes, which will be accurately measured by dual-energy X-ray absorptiometry (DXA). Although innovative techniques as bone microarchitecture analysis (BMA) and high-resolution peripheral quantitative computed tomography (HRpQCT) have been developed to provide not merely BMD, but also more detailed information about the bone microarchitectural properties, DXA remains the most widely used and most thoroughly studied bone density measurement technology in research as well as in clinical practice.^[35,36]^ As a sensitive technique for determining BMD, DXA may actually detect the minor changes of periprosthetic BMD after THA, and facilitate the evaluation of periprosthetic bone remodeling.^[22,37]^ We will use the metal removal analysis algorithms of the Hologic Discovery instrument (Hologic Inc, Waltham, MA) to measure the periprosthetic BMD in 7 conventional regions of interest (ROIs) based on Gruen zones, which is the most often used protocol in evaluation of bone remodeling after the implantation of conventional femoral stems.^[38,39]^ BMD in each Gruen zone will be measured 2 days postoperatively on both prosthetic side and contralateral side, which will be taken as baseline value for an exact longitudinal comparison. Index-ROIs of the Ribbed and LCU stems will be defined based on the 1st postoperative pattern, this reference allows us to minimize the inter-time point variability and assuring measurement precision (Figs. 3 and 4).

**Figure 3 F3:**
[figure not shown]
The defined Gruen zones of the periprosthetic side (Ribbed Hip system) and contralateral side.

